## Abstract

**Background:**

Systematic monitoring of work atmosphere and patient safety incidents is a necessary part of a quality assurance system, particularly an accredited system like the Joint Commission International (JCI). How the implementation of quality assurance systems affects well-being at work and patient safety is unclear. Evidence shows that accreditation improves workplace atmosphere and well-being. Thus, the assumption that an increase in employees’ well-being at work improves patient safety is reasonable.

**Objective:**

This study aims to describe the protocol for monitoring the effects of implementing the quality assurance system of JCI at Orton Orthopedic Hospital on employees’ well-being (primary outcome) and patient safety (secondary outcome).

**Methods:**

Quantitative (questionnaires and register data) and qualitative (semistructured interviews) methods will be used. In addition, quantitative data will be collected from register data. Both quantitative and register data will be analyzed. Register data analysis will be performed using generalized linear models with an appropriate distribution and link function. The study timeline covers the time before, during, and after the start of the accreditation process. The collected data will be used to compare job satisfaction, as a part of the well-being questionnaire, and the development of patient safety during the accreditation process.

**Results:**

The results of the quality assurance system implementation illuminate its possible effects on the patient’s safety and job satisfaction. The repeatability and internal consistency reliability of the well-being questionnaire will be reported. Data collection will begin in May, 2024. It will be followed by data analysis and the results are expected to be published by 2025.

**Conclusions:**

The planned study will contribute to the evaluation of the effects of JCI accreditation in terms of well-being at work and patient safety.

**International Registered Report Identifier (IRRID):**

PRR1-10.2196/45200

## Introduction

### Overview

Systematic monitoring of work atmosphere and patient safety incidents is a necessary part of a hospital’s quality assurance systems, particularly an accredited system like the Joint Commission International (JCI) [1,2]. Accreditation and related education have been shown to increase motivation and improve work atmosphere and awareness of patient safety. Statistically significant improvements have been noted in defect management (particularly in the context of instrument cleaning and disinfection effectiveness) in a randomized controlled trial evaluating the impact of JCI accreditation [3]. Physician-nurse relations as well as management-line staff relations have been reported to improve along accreditation [4].

Accreditation is a costly and time-consuming process [5], causing a legitimacy problem for a hospital’s management [6]. This situation raises a fundamental question: Is accreditation worth pursuing considering the time and effort it requires? Thus, further research is needed from a different view. How the implementation of quality assurance systems affects well-being at work and patient safety is not studied extensively [7]. The effects of quality assurance systems on work atmosphere and patient safety are challenging to determine due to numerous potentially confounding factors [8,9]. However, assuming that well-being at work and work satisfaction are strongly correlated with good outcomes in health care service delivery, including patient safety, is reasonable. This assumption is supported by Schwarz et al [10], who found that work-life integration among health care workers is associated with improvements in teamwork and safety across various safety culture domains [10]. In a study by Lopes et al [11], job satisfaction and safety culture were directly proportional. Better working conditions can provide a virtuous cycle of patient safety and occupational health [11].

The Finnish Institute of Occupational Health defines well-being at work as safe, healthy, and productive work, which is carried out by competent employees and work communities in a well-managed organization. Employees and work communities experience their work as meaningful and rewarding, and they consider work to support their life management [12]. The importance of well-being at work is highlighted in health care services, as labor input is directed toward patients. Well-being improves work performance, further promoting good workplace outcomes. For instance, well-being at work reduces the risks of exhaustion, workplace accidents, illnesses, and the loss of tacit knowledge regarding drug abuse [13]. The well-being of the working community is comprised of the performances of its members and linked to factors beyond each employee’s performance and influence. In this study, the operationalization of well-being is based on a model that considers worker health, subjective well-being, capabilities, motivation, the organizational management model, management workload, company values, and the overall atmosphere as well as the conditions of the work environment, such as work content and instruments with which the work is executed (Figure 1) [14].

**Figure 1 figure1:**
[figure not shown]
Domains well-being at work by Naumanen (2018) [14].

### Aim and Objectives

This protocol will describe the procedure and methods for monitoring the effects of implementing the quality assurance system of JCI at Orton Orthopedic Hospital on employees’ well-being (primary outcome) and patient safety (secondary outcome). The system implementation effects will be evaluated through work-related well-being surveys using direct and indirect evaluations, and patient safety will be evaluated using register data.

## Methods

### Overview

The study sample will include about 200 employees working in a hospital. The hospital is a private orthopedic hospital focused on joint replacements and back surgery and has a rehabilitation center. This hospital is owned by a large public health care hospital, which also performs JCI implementation. Table 1 illustrates the accreditation process and its monitoring. Textbox 1 [15] presents the registry data collection system. The implementation will begin following a JCI orientation training organized by JCI. The company must organize their employees during the process. The JCI procedure is designed to be ready in 4 years. Baseline surveys (questionnaires and interviews) will be conducted, and all surveys will be repeated when the implementation is 50% complete.

**Table 1 table1:** Methods and data collection system during the accreditation process.

Baseline surveys^a^	Data collection system
Questionnaires	A total of 35 questions; registering and monitoring the well-being of the employees of the Orton Orthopedic Hospital Repeatability test of the questionnaires
Register data	HaiPro^b^ Absence due to illness Employee turnover Injuries of the employees Cost of occupational health case Patient insurance cases Rate of wound infections Revisions Time of surgery
Qualitative method (semistructured interviews)	A total of 4 groups (doctors, nurses, therapists and administration, and support staff)

^a^Surveys, including questionnaires and register data, as well as qualitative methods (semistructured interviews) will be repeated after half of the implementation and after finishing accreditation.

^b^HaiPro is a web-based tool for reporting patient safety incidents. Anonymous and voluntary input ensures confidential reporting and processing of the safety incidents. The HaiPro method does not seek to blame [15].

Register data collection 2 years prior to implementation, when the implementation process is 50% complete, and when the facility is ready for accreditation. A web-based tool (HaiPro) will be used for reporting patient safety incidents and risk events, which are divided into near-miss and injurious events.
**Register data collection**
HaiPro—near-misses and misses (n)Absence due to illness (days)Employee turnover (n)Employee injuries (n)Cost of occupational health care (€/year)Patient insurance cases (n)Rate of wound infections (n)Time per surgery (h/min)Revision surgery (%)

### Quantitative Studies

#### Questionnaires

This study applies a mixed methods approach, including quantitative (questionnaires and register data) and qualitative (semistructured interviews) methods [16]. The study uses a convergent design, where both qualitative and quantitative data are collected as well as analyzed and results are reported at the same time [17]. The occupational well-being questionnaire in this hospital was developed before the planned study to facilitate good personnel management. In the questionnaire, job requirements and job resources have formed the theoretical framework of the survey [18-20]. It also included 4 questions designed to capture the participants’ views on leadership, values, expertise, and work atmosphere, based on Otala and Ahonen [21].

The questions are divided into 3 sections: questions 1-6 ask for the participants’ background information, questions 7-31 focus on physical and psychological well-being and connect to functional capacity, and questions 32-35 concern work satisfaction (Multimedia Appendix 1). The first section ascertains the employees’ health and well-being regarding work burden and the effects of illnesses and strains on functional capability. The questions will be evaluated on a 10-point Numeric Rating Scale (1=no work-related problems; 10=completely unable to work). Questions 7-21 evaluate perceived health and mood, distress, anxiety, and the ability to take care of oneself on a 3-point Likert scale (1=no problems; 3=completely unable). These questions are evaluated on a 5-point Likert scale (1=completely agree; 5=completely disagree).

In the third section, question 32 describes management from the viewpoint of an immediate superior. Question 33 explores the know-how viewpoint, aiming at charting the perspective to improve one’s competence and knowledge. Question 34 focuses on company values and acting upon them. Question 35 concerns team spirit, which is one of the company’s most important values. Questions 32-35 are evaluated on a 5-point Likert scale (1=completely agree; 5=completely disagree).

#### Register Data

Register data, including the employees’ sick leave and work accidents, will be collected from 2 years prior to implementation to 2 years after implementation. We will also use a web-based tool (HaiPro) for reporting patient safety incidents, which are all treatment events that either harmed or could have harmed them [15]. HaiPro is a web-based tool for reporting patient safety incidents. Anonymous and voluntary input ensures confidential reporting and processing of safety incidents and risk events. These events are called risk events and are divided into near-miss and injurious events [15]. In addition, the number of reoperations, the rate of wound infections, surgery times, and notices of injuries reported to the Finnish Patient Insurance Center will be collected. Textbox 1 shows the register data collection during the accreditation process.

### Qualitative Studies

Participants in the focus group interviews include working community members. The groups consist of multiprofessional individuals, and the interviews last about an hour. These qualitative interviews aim to broaden the baseline views, conceptions, and expectations of the personnel regarding quality assurance and their well-being before implementing the JCI quality assurance system. The semistructured interviews will be conducted by an external interviewer with knowledge of different quality assurance systems and conducting qualitative research.

Qualitative data are collected in 3 thematic group interviews that feature 12 participants. To create the groups for the interviews, a list of the hospital’s employees will be collected and grouped into 4 categories: physicians; nurses; therapists, other medical staff, and the administration; as well as support staff and secretaries. The personnel will be listed in each category in alphabetical order. Consequently, random selections will be made from the staff at the hospital, stratified by occupation, for all groups. After the draw, each employee can opt out of their assigned group. In such cases, the group is supplemented with the next person on the list. The researchers conducting this study are exempted from the lists. After 3 semistructured focus group interviews, the main themes will presumably recur, and the point of saturation will be reached [23].

The interviews will be recorded with the participant’s permission, and the tapes will be transcribed subsequently. The interviews will be analyzed using qualitative content analysis, a conventional content analysis [24]. The analysis aims to gain an understanding of how individuals in the small groups perceive the quality assurance system, assess its usefulness, and recognize the need for its development, all from the perspectives of different employees. The semistructured interviews ask participants about their expectations of the quality system, their involvement in the JCI orientation, as well as the perceived benefits and drawbacks of the quality system. In addition, the focus group interviews will ask about staff experiences in relation to safety, well-being, and motivation at work as well as the prospects of the hospital. The interviews will conclude with questions on quality factors related to surgery (eg, surgery times), patient safety, and experiences of patient care. Textbox 2 includes the semistructured interview questions.

The content of the open-ended questions will be coded according to the themes emerging from the data. The most prevalent themes will be selected and reported in the study. These themes will help explain and deepen the understanding of the responses to the quantitative approach of the study in describing the perceived conceptions of the quality system and its relationship to occupational safety, patient safety, and surgery.

The interviews will be renewed after half of the implementation is completed. The same groups will be requested to participate in the interviews; however, certain community members may change their working place or may not participate in the renewed test. Those members will be replaced by other members of the working community. If the point of saturation is not reached in the midterm interviews after 3 interviews, 4 or more interviews will be conducted [23].

Semistructured interview questions.
**Expectations from the quality assurance system, participation in orientation, perceived benefits of the quality assurance system, results, and their quality**
How have you participated in the quality assurance work?How have you experienced the training related to the quality assurance system and other orientations?What expectations do you have for the quality assurance system (ie, Joint Commission International)?What kind of benefits can the quality assurance system have? Do you think it might have some disadvantages as well?What kind of results can the quality assurance system have?How does it affect the quality of activities in the hospital?What kind of changes does the quality assurance system bring to your everyday work?In what state do you think the quality assurance system is right now?

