**Occupational well-being**
What do you perceive as factors related to well-being at work?What are the driving forces of occupational well-being in our hospital?What kind of effects the quality assurance system can have on well-being at work?Which aspects of occupational well-being are affected by the quality assurance system?

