In this protocol, the primary and secondary outcomes are well-being at work and patient safety, respectively. Patient safety has 4 main items: all the HaiPro notices [15], the number of wound infections, the number of patient insurance cases, and the number of revision surgeries. Certain overlaps exist between these items and must be considered in the analysis. Worker well-being register data will also be collected, including information on illness-related absences, employee turnover, employee injuries, and the costs of occupational health care.

A staff survey is an efficient way to learn the views of all personnel. Surveys also help employees evaluate their efforts and input [27]. Our study will use various evaluations. The most important variable is employee well-being, which is evaluated through the questionnaire. This questionnaire is specifically developed for the study and complemented with the register data follow-up regarding sick leave, employee turnover, and costs of occupational health care.

We acknowledge the problem of presenteeism, which involves the act or culture of employees continuing to work as a performative measure, despite negative consequences); this is a rising issue in the workplace. If left unrecognized and unresolved, presenteeism can lead to poor well-being, low morale, burnout, and increased employee turnover. It also poses a huge threat to productivity because employees who show up to work when they are not feeling mentally or physically well cannot provide their best performance [28]. Indirectly, the effects of presenteeism can be evaluated in this study using specific questionnaire items and register data. However, due to the absence of readily available indicators to apply here, a more comprehensive examination of the issue may be reserved for future studies.

We are aware that some parts of the accreditation are demanding and require going over the allotted work-hour resources. The hospital may have to spend additional time in ensuring the smooth operation of new formats. There might be a need for extra personnel for accreditation-related work. We have the approval from the hospital management and the commitment of the staff to this endeavor.

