Numerous confounding factors exist. Health care is greatly influenced by cultural norms and is strictly regulated by legislation. The strength of qualitative studies is to raise points of view that are formulated through study questions. The qualitative approach in research is exploratory and helps develop hypotheses for future studies. To the best of the authors’ knowledge, the combination of the qualitative and quantitative approaches (ie, mixed methods) has not been used in research on hospital accreditation.

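### The interview guide asks openly about benefits, asks about drawbacks only through one hedged yes/no question and never names workload, so the interviews risk under-representing drawbacks

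*Protocol article*

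**What the plan says.** The Qualitative Studies section lists what participants will be asked, including their expectations, their part in the orientation, "as well as the perceived benefits and drawbacks of the quality system". It points to Textbox 2 for the questions, so the wording is fixed in the article.

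In Textbox 2, benefits and drawbacks are taken together in one item: "What kind of benefits can the quality assurance system have? Do you think it might have some disadvantages as well". The heading of that block names "perceived benefits of the quality assurance system, results, and their quality" and does not mention drawbacks.

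The same section says that answers to the open-ended questions will be coded by the themes that emerge, and that the most frequent themes will be selected and reported. It states no provision for contrary or less frequent themes. The themes are meant to help explain the quantitative responses.

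Under Expected Outcomes, the protocol says that "some parts of the accreditation are demanding and require going over the allotted work-hour resources", and adds that extra personnel may be needed. The Introduction also calls accreditation costly and time-consuming and asks whether it is worth the effort.

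**The concern.** Paired questions about good and bad effects should be put in the same form. Here the first invites a list of benefits. The second asks whether there might be any disadvantages at all, as an addition to the first. A group can close that question with a short answer and move on. The burden that the protocol itself foresees, extra hours and possibly extra staff, has no question that names it.

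The reporting rule can then carry the imbalance forward. If drawbacks are raised less often because they were asked about less openly, a rule that keeps only the most frequent themes may drop them.

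What is at stake is how far the interviews can be relied on as explanation. The Limitations section offers the mixed-methods approach as the way to make up for having no comparison hospital, and the interviews are where staff are asked directly how the quality system affects their work. An account that leaves out part of the burden would bear on the protocol's own question of whether accreditation is worth its cost.

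**Working it through.** The plan gives no figure on this point, and no sample size or power calculation bears on it. The check is a count of every question in Textbox 2, each classed by the direction of its wording.

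**Inputs: questions per block of Textbox 2**

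| Block | Questions |
|---|---|
| Expectations, orientation, benefits, results | 9 |
| Occupational safety, motivation, prospects | 2 |
| Occupational well-being | 4 |
| Surgery, patient safety, patient care | 6 |
| Total | 9 + 2 + 4 + 6 = 21 |

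The benefits/disadvantages item holds two questions and is counted as two.

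**Classification**

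| Wording | Count | Share of 21 |
|---|---|---|
| Favourable, about the quality system, open (benefits) | 1 | 4.8% |
| Favourable, about well-being in the hospital generally, open (driving forces) | 1 | 4.8% |
| Unfavourable, about the quality system, hedged yes/no (disadvantages) | 1 | 4.8% |
| No direction | 18 | 85.7% |

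Check: 1 + 1 + 1 + 18 = 21.

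Of the 18 questions without direction, 12 ask about results, changes or effects of the system; 4 about participation, training, expectations and current state; 1 about factors in well-being; and 1 is the closing invitation to add anything else. Check: 12 + 4 + 1 + 1 = 18.

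**What follows from the count**

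- *Number.* Questions that name benefits of the system and questions that name its drawbacks stand 1 to 1. There is no imbalance in number.
- *Form.* The other 20 questions open with what, how, which or in what state. The drawback question is the only one in yes/no form, so the single unfavourable prompt is also the single closed prompt.
- *Workload.* Questions naming workload, overtime or time cost to staff: 0 of 21. Surgery times are asked about, but as a quality measure of surgery.
- *Time to probe.* Interviews last about an hour. If the time were spread evenly, 60 / 21 = 2.9 minutes per question, shared across the group. The even split is an assumption, used only to show that there is limited room for unscripted follow-up.

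**Passages side by side.** The text names benefits and drawbacks together; the block heading names benefits alone; the question pair differs in form; the Discussion expects extra hours and the guide does not name them. How far this would move the frequency of themes cannot be calculated, because it depends on what participants say and how the interviewer follows up.

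**The case against.** The strongest reply is that most of the guide is neutral. Staff can speak of extra work in answer to "What kind of changes does the quality assurance system bring to your everyday work", to "What kind of effects the quality assurance system can have on well-being at work", to the question on motivation or to the closing question. The format is semistructured and led by an outside interviewer with experience of qualitative research. In a group, a question about possible disadvantages may work as an invitation to discuss, and follow-up probes are commonly left out of an article. Themes are topics and not votes for or against: a workload theme raised by most participants would be reported.

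Much of this stands, and it rules out several stronger readings that a reader might infer.

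- *That favourable themes are bound to dominate.* With 18 of 21 questions free of direction and explicit prompts at 1 to 1, the wording does not fix the result.
- *That the question "What are the driving forces of occupational well-being in our hospital" adds a second prompt in favour of accreditation.* It concerns well-being in the hospital generally, and it follows a neutral question on factors related to well-being, under which hindrances can be raised.
- *That the protocol promises equal weight and breaks the promise.* It says only that both benefits and drawbacks are asked about, and both are. There is no outright contradiction.
- *That the protocol admits its questions determine the answers.* The remark that qualitative studies "raise points of view that are formulated through study questions" is offered as a strength of the method, not as a concession.
- *That the primary outcome is biased.* Well-being is evaluated by the questionnaire, complemented by register data. The interviews are explanatory and are described as exploratory.

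The reply does not remove the difference in form between the two questions, the absence of any question naming a burden that the protocol expects, or the reporting rule that keeps only common themes. Probing might make up for the wording, but the document describes no probes.

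**Conclusion.** The point holds as a risk of leading-question bias in the interview component. One question of 21 asks about drawbacks, in hedged yes/no form, against one open question on benefits; none names workload or time. Reporting only the most frequent themes makes it more likely that any under-prompted drawback is lost. The likely direction is towards a more favourable picture of the quality system, but neither the direction nor the size of the result is fixed by the guide.

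This rests on two assumptions: that the interviewer keeps broadly to the printed questions, and that a closed, hedged prompt draws less discussion than an open one. If undisclosed probes on drawbacks and workload exist, the risk is smaller. The point is confined to the interviews and to the use of their themes to explain the quantitative results. It is worth acting on mainly because the correction is nearly free.

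**What to change.** Before the first wave of interviews:

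1. Replace the benefits/disadvantages pair with two questions of the same form, for example: *What benefits, if any, can the quality assurance system have?* and *What drawbacks, if any, including workload and time, can it have?* Naming workload and time is justified because the protocol itself expects this burden.
2. Add drawbacks to the heading of that block, so that it matches the text.
3. Use the same wording in every wave. A change between waves would be mixed up with any change in staff views. If the baseline interviews have already been held, state the change of wording wherever waves are compared.
4. Add to the reporting rule that contrary or less frequent themes will be reported beside the most frequent ones.

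The cost is the rewording of existing prompts and slightly longer reporting. The guide stays about the same length, and no extra interviews or staff are needed.
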